#### **4.8.3 Control protocol**

The newborns in the control group will undergo the same kangaroo positioning procedures described earlier but will not receive the physiotherapy intervention protocol. Thus, the newborn will be positioned in the incubator/crib before being placed in the kangaroo position with the mother.

### **4.9 Outcomes**

#### **4.9.1 Primary outcomes**

- **Weight Gain:** daily body weight recording as a parameter for weight tracking of preterm newborns during the application of the protocol (experimental and control).
- **Neuromotor Behavior:** assessed by the classifications of GMs achieved using the GMA (EINSPIELER et al., 1997).

#### **4.9.2 Secondary outcomes**

- **Posture and Muscle Tone:** behavior regarding posture and muscle tone, assessed by the classification achieved using the neurological signs evaluation method from the neonatal neuromotor screening (GONÇALVES, 2012).
- **Behavioral State:** Behavioral state according to the adapted Brazelton scale (BRAZELTON et al., 1976).

- **Time to Establish Breastfeeding:** defined as the interval in days between the start of the protocol and successful breastfeeding at the breast. Success in breastfeeding will be considered according to the main key points for proper positioning and latch during the feeding: the baby's face facing the breast, with the nose at nipple level, the baby's body close to the mother's, with the baby's head and torso aligned; the baby well supported; more areola visible above the baby's mouth; mouth wide open; lower lip turned outward; and the chin touching the breast (BRASIL, 2011a).
- **Exclusive Breastfeeding Maintenance:** defined as the continuation of exclusive breastfeeding at corrected ages of 2 weeks post-term, 12 weeks post-term, and at 6 months, being dichotomous.
- **Hospitalization Time:** defined as the average number of days the newborn stays in the hospital environment.
- **Degree of Respiratory Distress** obtained by summing the score according to the BSA (SILVERMAN; ANDERSEN, 1956; BRASIL, 2011b) on each day of the protocol.
- **Physiological Parameters** (heart rate, respiratory rate, peripheral oxygen saturation, body temperature): vital signs evaluated and recorded before and after the protocol (experimental and control) each day.

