### **4.2 Participants**

This study will involve 34 preterm newborns, born with a gestational age of 34 weeks or less, between 34 and 36 weeks and 6 days postmenstrual age, hospitalized in the Neonatal Intermediate Care Unit (UCIN). To estimate the minimum number of participants, considering a difference of at least 50% between the groups regarding the quality of general movements (GMs) after the intervention using the chi-square test, the suggested sample size is 13 participants per group (80% power;  $\alpha = 5\%$ ). Considering potential losses during the follow-up, two groups of 17 participants will be included. The newborns will be randomly allocated into two groups: the experimental group ( $n=17$ ), which will receive the physiotherapy intervention protocol associated with the kangaroo position, and the control group ( $n=17$ ), which will receive only the kangaroo position.

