### **4.3 Inclusion criteria**

Preterm newborns will be included in the study if they meet the following criteria: gestational age at birth equal to or less than 34 weeks, more than 72 hours of postnatal life, hospitalized in the Neonatal Intermediate Care Unit (UCIN), clinically stable, general

movements with a poor repertoire, no need for invasive or non-invasive mechanical ventilation, may require oxygen support via nasal cannula, residents of Campo Grande-MS (Brazil).

Medical records, nursing notes, physiotherapy records, and the recommendations from neonatologists and the multidisciplinary team will be used as the reference for the selection or exclusion of patients based on the criteria described above.

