#### **4.8.2 Procedures of randomization and allocation**

The distribution of newborns into groups will be random, following a prior computational randomization in blocks of 4 babies for each group. The allocation to the groups will be concealed from the researchers involved through individual opaque, sealed, and sequentially numbered envelopes. The envelopes will be opened before the experimental or control protocol is performed, according to the inclusion of the babies in the study. The evaluations for GMs will be filmed and scored later, without identifying the allocation of the newborns in the groups, allowing for a subsequent blinded assessment.

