#### **4.8.4 Data collection and testing procedures**

The clinical history data of the newborns will initially be recorded on a medical history form, collecting information regarding the newborn's eligibility criteria for the study. Data of both the newborn and the mothers will be obtained from medical records, nursing notes, physiotherapy records, and the child's health booklet.

The number of days from the start of the protocol until the establishment of breastfeeding will be recorded, along with the period of breastfeeding maintenance in days until hospital discharge. The continuation of exclusive breastfeeding after discharge will also be assessed at 12 weeks post-term. For these records, the mother and the multidisciplinary team will be consulted. Additionally, the daily body weight of the newborns will be recorded until the completion of the protocol, as well as the total length of hospital stay.

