
#### *4.8.5.2 Kangaroo Position protocol*

In the kangaroo position, the newborn should be placed only in a diaper in a vertical or elevated diagonal position, between the mother's breasts, with the head laterally positioned, upper and lower limbs in flexion and adduction. The mother should not wear a bra and should be dressed in a gown with a front opening. After positioning the baby, the mother should cover

him with the gown, and then the dyad should be secured with a moldable cotton band for additional safety (BRASIL, 2013).

The experimental protocol will begin when the baby reaches 34 weeks of postmenstrual age, has been alive for more than 72 hours, weighs over 1100g, and is clinically stable, respecting signs of stress (DUARTE et al., 2011). It will be conducted during the following 15 days. By the end of the protocol, each newborn will have received 15 sessions of the physiotherapeutic protocol combined with the kangaroo position. The interventions will be scheduled during the intervals between feeding times (oral or via tube). Stress factors such as noise and lighting will be minimized during the experimental and control protocols. The procedure will only be conducted after the newborn has been fed, waiting at least 60 minutes after feeding.

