#### 4.10 Data Analysis

For the statistical analysis of the data, the statistical package SPSS 23.0 will be used. To analyze the dependent variables, the Levene's Test for Homogeneity of Variance and the Shapiro–Wilk Test for Normality will be applied. Once the assumptions are met, parametric and non-parametric tests may be applied depending on the homogeneity and normality conditions of the sample. Descriptive statistics will first be performed to characterize the sample. Treatment effects will be obtained by comparing the groups

To test differences between groups (treatment effects) for categorical variables (quality of GMs, behavioral state, success, and maintenance of breastfeeding), the chi-square test will be applied. To test differences between groups concerning body weight, the independent t-test will be used. For other continuous variables, t-tests or the Mann–Whitney test will be used to calculate differences between the groups. Adjusted means and 95% confidence intervals may also be calculated using the mixed linear model (GLM) for continuous variables, considering the interaction terms of group x days of evaluation.

To calculate the effect size of the intervention, a 95% confidence interval will be adopted, and either Cohen's d or r ( $r = \text{z-score} / \sqrt{\text{total sample}}$ ) will be considered, depending

on whether parametric or non-parametric tests are used. A significance level of  $\alpha=5\%$  will be considered for all analyses.

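### Hospital stay is counted in total, so it carries pre-allocation days that add noise, and time to breastfeeding has no rule for infants who never establish it

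*Protocol*

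**What the plan says.** **Hospital stay.** Section 4.9.2 of the protocol lists hospitalization time as a secondary outcome, "defined as the average number of days the newborn stays in the hospital environment". No start date is given. Section 4.8.4 settles what is collected: daily weight until the protocol is complete, "as well as the total length of hospital stay".

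**When infants enter.** Section 4.3 requires "gestational age at birth equal to or less than 34 weeks, more than 72 hours of postnatal life", with no lower limit on gestation. Section 4.8.5.2 says "The experimental protocol will begin when the baby reaches 34 weeks of postmenstrual age", and section 4.2 places participants "between 34 and 36 weeks and 6 days postmenstrual age". On allocation, section 4.8.2 says "The envelopes will be opened before the experimental or control protocol is performed". Randomisation is in blocks of 4, and no stratification by gestation is stated.

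**Breastfeeding.** Section 4.9.2 has time to establish breastfeeding "defined as the interval in days between the start of the protocol and successful breastfeeding at the breast". It gives no value, censoring time or rank for an infant who never succeeds.

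**Analysis.** Section 4.10 states that for continuous variables other than body weight "t-tests or the Mann–Whitney test will be used to calculate differences between the groups". Adjusted means from a mixed model are optional, and the only terms named are group by day of evaluation. Breastfeeding success and its maintenance are compared by chi-square.

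**The concern.** Both outcomes are specific objectives in section 3.2, and both are handled so that the planned comparison is weaker than the collected data allow.

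For stay, an infant born at 28 weeks brings about 42 days that precede allocation, and one born close to 34 weeks brings only a few. The variation comes from gestation at birth and is fixed before the envelope is opened. With 17 infants per arm, it widens the interval around any treatment effect and lets chance differences in gestation show up as differences in stay. The breastfeeding interval in the same list is anchored to the start of the protocol; the stay outcome is not.

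For breastfeeding, infants without an event are those with the worst result. If the test uses only infants who have a value, the comparison is made in a group selected after randomisation, and the selection may differ between arms.

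**Working it through.** **Stated sample size.** The protocol sizes the trial only on general movements: 13 per group, raised to 17 for losses. The 13 is consistent with a two-proportion formula for a 50-point difference, which gives 11 to 15 per group depending on the base rate. It has no bearing on these two outcomes, for which the protocol gives no SD, target effect or event rate. Those inputs are assumptions below.

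**Hospital stay**

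Inputs:
- From the protocol: 17 per arm, 5% significance level (two-sided assumed), 80% power, more than 72 hours of life at entry, start at 34 weeks.
- Assumed: gestation at birth spread evenly from a lower limit L to 34 weeks, and a post-start SD of 7 or 14 days, independent of gestation.

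Days before the start then run from 3 to 7 × (34 − L), approximately uniform. So:
- SD before start = (7 × (34 − L) − 3) / √12
- SD of total stay = √(SD before² + SD after²)
- Detectable difference with 17 per arm = 0.991 × SD (two-sample t-test)

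For L = 28: (42 − 3)/√12 = 11.3; √(11.3² + 7²) = 13.3; 0.991 × 13.3 gives 13.1 days from unrounded values. Counted from the start: 0.991 × 7 = 6.9 days.

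| Births (weeks) | SD before start | Variance ratio, SD after 7 | Detectable, SD after 7 | Variance ratio, SD after 14 | Detectable, SD after 14 |
|---|---|---|---|---|---|
| Counted from start | – | 1 | 6.9 | 1 | 13.9 |
| 32–34 | 3.2 | 1.2 | 7.6 | 1.05 | 14.2 |
| 30–34 | 7.2 | 2.1 | 10.0 | 1.3 | 15.6 |
| 28–34 | 11.3 | 3.6 | 13.1 | 1.65 | 17.8 |
| 26–34 | 15.3 | 5.8 | 16.7 | 2.2 | 20.6 |

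The variance ratio is (SD before² + SD after²)/SD after². For example, 32–34 weeks with SD 14 gives (3.2² + 14²)/14² = 1.05.

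**Time to breastfeeding**

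All rates are assumed, with 17 per arm. The Mann–Whitney figures are from simulation, and the chi-square is uncorrected.

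| Never establish, control v treated | Times among establishers | Mann–Whitney, establishers only | Mann–Whitney, never-establishers ranked worst | Chi-square on success |
|---|---|---|---|---|
| 35% v 10% | equal | 5% | 23–24% | 41% |
| 50% v 5% | equal | 5% | 63–66% | 89% |
| 50% v 10% | means 8 v 6 days, SD 3 | 28% | 86% | 75% |
| 10% v 10% | means 8 v 6 days, SD 3 | 40% | 31% | 3% |

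Where the arms differ only in who succeeds (first two rows), the establishers-only test rejects at its nominal 5%, so it carries no information on the benefit. The chi-square on success does, and it has more power there than the worst-rank test. Where treatment improves both success and speed (third row), the worst-rank test is the strongest and the establishers-only test loses most of the signal. Where success is equal and only speed differs (last row), the establishers-only test is somewhat stronger. The case for keeping all infants is therefore that the comparison stays randomised, not that it always gains power.

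**The case against.** **Stay.** Allocation is random and concealed, so the pre-allocation days are balanced in expectation and total stay is an unbiased endpoint. The size of the loss depends wholly on inputs the protocol does not give. If nearly all births fall at 32–34 weeks, the detectable difference moves only from 6.9 to 7.6 days, or from 13.9 to 14.2 with the larger SD. All of this stands. A reader might infer that the pre-allocation weeks swamp any effect or bias the comparison. The documents do not support that, because they give no gestation distribution, and randomisation rules out systematic error from this source. The optional adjusted means could recover some precision, but no gestation covariate is named.

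**Breastfeeding.** The protocol nowhere says that infants who never establish breastfeeding are excluded, and Mann–Whitney is compatible with a worst rank. A handling rule could be added in a statistical analysis plan that is not shown. A reader might also infer that a real benefit in reaching breastfeeding would vanish from the results. That goes too far: section 4.10 plans a chi-square on success, which retains these infants and detects such a benefit with 41% and 89% power in the first two scenarios. What remains is narrower. The protocol fixes both the definition of the interval and the tests, and applied as written they use only infants with a value. The chi-square answers a different question and leaves the time comparison on a selected subset.

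**Conclusion.** The point holds as a matter of efficiency and definition in two secondary outcomes; the priority is minor to moderate. Weight gain and general movements, the primary outcomes, are not affected.

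Counting total stay inflates the variance by a factor between 1.05 (births 32–34 weeks, post-start SD 14 days) and 5.8 (births 26–34 weeks, post-start SD 7 days). The direction is certain if stay after the start is unrelated to gestation at birth, as assumed here. The size is not known from the protocol and would be small in a cohort born mostly at 32–34 weeks.

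For breastfeeding, the definition leaves infants who never succeed without a value, so the stated tests by default compare establishers only. That they would be dropped follows from the definition and is not stated. The consequence is limited to the time comparison, because success is tested separately.

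**What to change.** 1. In section 4.9.2, define the compared hospital stay as days from randomisation (or protocol start) to discharge, and report total stay descriptively.
2. In section 4.10, analyse time to breastfeeding on all randomised infants, either by Kaplan–Meier and log-rank from protocol start, or by Mann–Whitney with infants who never establish it before discharge given the worst rank. State the choice before the data are examined. If log-rank is used, also state how an infant discharged without breastfeeding is treated, since censoring at the infant's own discharge would assume the same later chance of success as for those still in hospital.
3. Keep the chi-square on success alongside it.

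The cost is a few lines of wording. The plan already records days from protocol start and length of stay, so no extra data, visits or infants are needed.

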#### 4.10 Data Analysis

For the statistical analysis of the data, the statistical package SPSS 23.0 will be used. To analyze the dependent variables, the Levene's Test for Homogeneity of Variance and the Shapiro–Wilk Test for Normality will be applied. Once the assumptions are met, parametric and non-parametric tests may be applied depending on the homogeneity and normality conditions of the sample. Descriptive statistics will first be performed to characterize the sample. Treatment effects will be obtained by comparing the groups

To test differences between groups (treatment effects) for categorical variables (quality of GMs, behavioral state, success, and maintenance of breastfeeding), the chi-square test will be applied. To test differences between groups concerning body weight, the independent t-test will be used. For other continuous variables, t-tests or the Mann–Whitney test will be used to calculate differences between the groups. Adjusted means and 95% confidence intervals may also be calculated using the mixed linear model (GLM) for continuous variables, considering the interaction terms of group x days of evaluation.

To calculate the effect size of the intervention, a 95% confidence interval will be adopted, and either Cohen's d or r ( $r = \text{z-score} / \sqrt{\text{total sample}}$ ) will be considered, depending

on whether parametric or non-parametric tests are used. A significance level of  $\alpha=5\%$  will be considered for all analyses.

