### **Abstract**

Preterm newborns are vulnerable to perinatal conditions due to their organic immaturity and associated external factors. This association can lead to neurological impairments, affecting motor development, respiratory mechanics, and the establishment of breastfeeding. Considering the current approach to the humanization of neonatal care, as well as the recent Brazilian epidemiological need for studies focused on early intervention in hospitalized newborns at risk or with established neurological problems, the necessity for therapeutic investigations that help prevent and minimize morbidities in this population becomes evident. The primary objective of this study is to evaluate the short- and medium-term effects of a physiotherapeutic intervention protocol associated with kangaroo positioning on the neuromotor behavior and clinical outcomes of preterm newborns in a neonatal unit. A randomized controlled trial with a parallel group design and balanced distribution ratio will be conducted. A total of 34 preterm newborns, with more than 72 hours of postnatal life and stable clinical conditions, admitted to Neonatal Intermediate Care Units will participate in this study. They will be randomly divided into two groups: a) Experimental Group (EG), which will receive the physiotherapeutic intervention protocol associated with kangaroo positioning; and b) Control Group (CG), which will receive only the kangaroo position. The protocol will be implemented over 10 consecutive days, with each session of the physiotherapeutic intervention lasting 15 minutes and 60 minutes of kangaroo positioning, during the period from 34 to 36 weeks and 6 days of postmenstrual age. Primary outcomes will include weight gain at the end of the protocol; Prechtl's general movements assessment at 36 weeks postmenstrual and 12 weeks post-term. Secondary outcomes will include posture and muscle tone, behavioral state, time to establish and maintain breastfeeding, duration of hospitalization, and vital signs. This study will provide experimental support for evidence-based practice, and its results may be used to guide feasible intervention protocols for the routines of neonatal unit teams in Brazilian hospitals.

**Keywords:** Early stimulation. Kangaroo method. Preterm newborn. Child development.

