#### 4.7.3 Brazelton's Neonatal Behavioral State

The adapted Brazelton's Neonatal Behavioral Assessment Scale was used to assess behavioral state. The scale categorizes the newborn's behavior based on their current state,

ranging from 1 to 6. State 1: deep sleep, still with steady breathing; State 2: light or active sleep, eyes closed with occasional body movements; State 3: drowsy, intermittently opening and closing the eyes; State 4: quietly alert, minimal physical activity; State 5: fully awake with energetic movements (active alert); State 6: crying (BRAZELTON et al., 1976).

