##### *4.8.4.1. Assessments at the UCIN*

The preterm newborns in both the experimental and control groups will be evaluated by the researcher in the NICU regarding respiratory discomfort at two time-points: I) before the

start of the protocol (experimental or control), with the baby still in the incubator/crib (Day 1); and II) after the completion of the protocol with the baby positioned in the incubator/crib (Day 15).

Physiological parameters (heart rate, respiratory rate, peripheral oxygen saturation, body temperature) and behavioral state will be assessed at three-time points daily: I) immediately before the protocol (experimental or control), with the baby still in the incubator/crib; II) 60 minutes after the start of the kangaroo position (experimental or control), while the baby remains in the position; and III) 30 minutes following, with the baby repositioned in the incubator/crib.

GMs and neuromotor screening (posture and tone) will be evaluated at two time-points: I) one day before the start of the protocol; and II) one day after the completion of the protocol.

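### Section 4.10 assigns a chi-square test to behavioural state, which is read 30 or 45 times per infant, without stating the unit of analysis

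*Protocol*

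**What the plan says.** - **Outcome.** Section 4.9.2 lists behavioural state as a secondary outcome on the adapted Brazelton scale. Section 4.7.3 describes the scale as "ranging from 1 to 6", from deep sleep to crying. Neither section names a time point or a summary for analysis.
- **Collection.** Section 4.8.4.1: "behavioral state will be assessed at three-time points daily". The three points are before the session, 60 minutes into the kangaroo position, and 30 minutes later with the infant back in the incubator or crib. Vital signs follow the same schedule there.
- **Duration.** The Abstract says "The protocol will be implemented over 10 consecutive days", and section 3.1 also gives ten days. Section 4.8.5.2 says "By the end of the protocol, each newborn will have received 15 sessions", and the hypothesis in the Introduction and the Day 15 assessment in section 4.8.4.1 agree with that. These places must be reconciled.
- **Test.** Section 4.10: "for categorical variables (quality of GMs, behavioral state, success, and maintenance of breastfeeding), the chi-square test will be applied". For continuous variables other than body weight, "t-tests or the Mann–Whitney test will be used to calculate differences between the groups".
- **Repeated measures.** Section 4.10 allows, but does not require, adjusted means "using the mixed linear model (GLM) for continuous variables, considering the interaction terms of group x days of evaluation". It names no such method for a categorical outcome.
- **Error level.** Section 4.10 sets a significance level of 5%, which "will be considered for all analyses".

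**The concern.** The chi-square test of two groups assumes that every count in the table is an independent observation. Allocation is by infant, and readings from one infant tend to resemble each other, so the infant is the independent unit. With 30 or 45 readings per infant and no stated rule for reducing them to one, the test in section 4.10 cannot be applied until someone makes a choice that the protocol leaves open. The available choices have very different error rates, and the choice could be made after the data are seen.

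What is at stake is a false claim about behavioural state. That outcome appears in the first research question of the Introduction, has its own specific objective in section 3.2, and feeds results meant to support use of the protocol at both hospitals.

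**Working it through.** **Inputs from the protocol.** 34 infants, 17 per group (4.2); 3 readings a day (4.8.4.1); 10 or 15 days (see above); 6 states (4.7.3); alpha 5% (4.10).

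**Inputs assumed.** The ICC, 0.02 to 0.30. For the simulation, also the state frequencies: 60/40 for a two-level state, and 20, 35, 15, 15, 10 and 5% for six states.

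**Step 1: readings.** 3 x 10 = 30 or 3 x 15 = 45 per infant. With no losses, 34 x 30 = 1,020 or 34 x 45 = 1,530 in all.

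**Step 2: the plan's own figure.** The only error rate stated for this analysis is the nominal 5%. With one reading per infant and 17 per group, simulation (10,000 runs) gives about 5% for a two-level state and about 3% for six states. The second is low because the table is sparse. With 13 per group the figures are about 7% and 3%. So the test behaves acceptably when each infant counts once.

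**Step 3: if all readings are pooled.** With m readings per infant, the design effect is DE = 1 + (m - 1) x ICC. At ICC 0.10:

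- m = 30: DE = 1 + 29 x 0.10 = 3.9
- m = 45: DE = 1 + 44 x 0.10 = 5.4

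The type I error is 2 x (1 - Phi(1.96 / sqrt(DE))) for two levels and P(chi-square on 5 df > 11.07 / DE) for six states. For two levels at DE = 3.9, 1.96 / 1.975 = 0.992, which gives 32%. At DE = 5.4, 1.96 / 2.324 = 0.843, which gives 40%.

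| State scale, m | ICC 0.02 | 0.05 | 0.10 | 0.20 | 0.30 |
|---|---|---|---|---|---|
| Two levels, 30 | 12% | 21% | 32% | 45% | 53% |
| Two levels, 45 | 15% | 27% | 40% | 53% | 60% |
| Six states, 30 | 22% | 48% | 72% | 90% | 95% |
| Six states, 45 | 32% | 63% | 84% | 95% | 98% |

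A Dirichlet-multinomial simulation with 13 and 17 infants per group agrees within about 1 to 2 points.

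**Step 4: if readings are pooled within one of the three daily time points.** Then m = 10 or 15. For two levels at ICC 0.05 to 0.30, the type I error is 10-31% (m = 10) or 13-39% (m = 15).

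**Step 5: if each occasion is tested separately.** Independence between infants holds, but there are 30 or 45 tests. A 2 x 6 table of 34 infants averages 34 / 12 = 2.8 per cell.

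- At an exact 5%, the expected false positives are 30 x 0.05 = 1.5 or 45 x 0.05 = 2.25. If the tests were independent, the chance of at least one would be 1 - 0.95^30 = 79% or 1 - 0.95^45 = 90%.
- At the 3% that the sparse six-state table delivers, the expected numbers are 0.9 or 1.35 and the chances 1 - 0.97^30 = 60% or 1 - 0.97^45 = 75%.

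The tests reuse the same infants, so the chances calculated under independence are best read as upper figures.

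**Step 6: if there is one value per infant.** This is valid, but no such value is defined. A natural one, such as the share of readings in certain states, is not categorical, so chi-square would no longer be the test.

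**The case against.** The strongest reply is that section 4.10 never says that all readings go into one table. A reader might infer from the named test that repeated readings will be counted as separate infants and that the plan therefore carries a 20-60% false-positive rate. The text does not support that. The same list holds general-movement quality and breastfeeding maintenance, each assessed on a few separate occasions, so comparison occasion by occasion is a natural reading. The authors also include group-by-day terms for continuous outcomes, so they recognise the repeated structure. The 20-60% range needs three things that are not in the documents: full pooling, an ICC of 0.05-0.30, and a two-level state. Full pooling would also mix pre-session with later readings, an unlikely way to look for a treatment effect. All of this stands, and the size must be given as conditional.

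A second reply is that the unit of analysis of a secondary outcome is commonly left to the SAP, which is not at hand. This stands only in part. The protocol does not leave the method open: it commits to a test, and a SAP that kept that test would still have to choose among steps 3, 5 and 6.

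A third is that vital signs do not belong here, because a mixed model is already offered for them. That limb is indeed weaker, and none of the calculations concerns it. The point there is only that the suitable model is optional, while the two-group tests are the stated analysis. Section 4.9.2 also describes vital signs as recorded before and after each session, against three points in section 4.8.4.1.

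A complaint that chi-square ignores the order of the six states is secondary. The documents set no direction of benefit along the scale, and the conclusion does not rely on it.

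**Conclusion.** The point holds as a mismatch between a named test and the data collected. Chi-square is assigned to an outcome with 30 or 45 readings per infant, the unit of analysis is not stated, and the only model for repeated readings is optional and excludes categorical outcomes.

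The consequence is conditional. Pooling would raise the type I error above 5%, modestly at an ICC of 0.02 and severely from 0.05 upward, and more so on the six-state scale than for two levels. Separate tests would avoid the independence error but bring uncorrected multiplicity and sparse tables. One value per infant would remove the inflation. The ICCs and state frequencies are assumptions, and no single error rate can be attributed to the plan as written.

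The outcome is secondary. The primary outcomes, weight gain and general movements, are not affected. It should be corrected, but it does not threaten the trial's main comparison.

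**What to change.** In section 4.10, take behavioural state off the chi-square list and name one of these:

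1. A repeated-measures binary or ordinal model clustered on infant (GEE or mixed model), with group, time point, day and pre-session state as terms. With at most 34 infants, GEE standard errors should carry a small-sample correction.
2. One predefined summary per infant, for example the share of post-session readings in a pre-named set of states, compared by the Mann-Whitney test.

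For the daily vital signs, make the mixed model that section 4.10 already mentions, with infant as a random effect, the stated analysis rather than an option. Reconcile the 10-day and 15-day statements so that the number of readings per infant is fixed.

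The cost is a few lines of text and modest analysis work, with no new data. Confidence intervals will be wider than under pooling.

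### Weight gain is a primary outcome, but the only committed test is an unadjusted t-test on body weight; gain should be defined and the comparison adjusted for Day-1 weight

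*Protocol*

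**What the plan says.** The Abstract states that "Primary outcomes will include weight gain at the end of the protocol", and the Specific objectives (3.2) also speak of weight gain. Section 4.9.1 heads the outcome Weight Gain but describes it only as "daily body weight recording as a parameter for weight tracking of preterm newborns during the application of the protocol". It gives no formula for gain and no time point.

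Section 4.8.4 states that "the daily body weight of the newborns will be recorded until the completion of the protocol", so a starting weight should be on file for every infant.

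The committed analysis is in section 4.10: "To test differences between groups concerning body weight, the independent t-test will be used". The same section adds: "Adjusted means and 95% confidence intervals may also be calculated using the mixed linear model (GLM) for continuous variables". That model is described with group-by-day interaction terms. It is permitted, not required, and no baseline covariate is named.

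The sample size in section 4.2 rests on general movements alone. No SD, correlation, target difference or power is given for weight.

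**The concern.** The outcome is a change, but the variable named in the committed test is a level. An infant's weight at the end of the protocol depends heavily on its weight at the start, and the eligible range is wide. Birth is at 34 weeks or less with no stated lower limit (4.3), and weight at the start is above 1100 g with no stated upper limit (4.8.5.2). Section 4.8.2 describes block randomisation and names no stratification by weight. With 17 infants per arm, a chance difference in starting weight between the arms is easily large enough to matter.

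If raw end weight is compared, that variation stays in the error term, although the measurement that would remove it is already being collected. At stake is the ability of a small trial to see a weight effect on one of its two primary outcomes, and whether the reported comparison is one of weight gain at all.

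**Working it through.** **The plan's own figure.** Section 4.2 gives 13 per group for general movements, "considering a difference of at least 50% between the groups regarding the quality of general movements (GMs) after the intervention using the chi-square test". The pooled two-proportion formula is n = [1.96·√(2p̄(1−p̄)) + 0.8416·√(p₁(1−p₁)+p₂(1−p₂))]² / 0.5².
- 0% against 50%: (1.200 + 0.421)²/0.25 = 10.5, so 11.
- 10% against 60%: (1.322 + 0.483)²/0.25 = 13.04, so 14.
- 25% against 75%: (1.386 + 0.515)²/0.25 = 14.5, so 15.

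The stated 13 is within two infants of each. It carries no information about weight.

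**Inputs for weight.** From the protocol: 17 per arm (4.2) and alpha 5% (4.10), taken as two-sided. Assumed, because the protocol gives none: SD of weight s = 300 g (range 200 to 350 g), correlation of Day-1 and final weight r = 0.80 to 0.95, and a true difference of 100 g for illustration.

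**Standard error of the difference between arms, s = 300 g.**
- End weight, unadjusted: s√(2/17) = 300 × 0.343 = 102.9 g.
- Gain, t-test: 102.9 × √(2(1−r)).
- ANCOVA with Day-1 weight: 102.9 × √(1−r²), before the cost of estimating the slope.

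| r | End weight | Gain | ANCOVA |
|---|---|---|---|
| 0.80 | 102.9 g | 65.1 g | 61.7 g |
| 0.90 | 102.9 g | 46.0 g | 44.9 g |
| 0.95 | 102.9 g | 32.5 g | 32.1 g |

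**Power for 100 g (noncentral t, 17 per arm, s = 300 g, r = 0.90).** End weight 16%, gain 56%, ANCOVA 58%. By the normal approximation, 80% power would need 142, 29 and 27 infants per arm respectively. Over s = 200 to 350 g and r = 0.80 to 0.95, power is 13–29% for end weight, 25–99% for gain and 27–99% for ANCOVA.

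**ANCOVA against gain, counting slope estimation.** With 34 infants, estimating the slope inflates the ANCOVA variance by about 1 + 1/30 = 1.033. The variance ratio of gain to ANCOVA is then [2/(1+r)]/1.033.
- r = 0.80: 1.111/1.033 = 1.075, about 7% less variance with ANCOVA.
- r = 0.90: 1.053/1.033 = 1.019, about 2% less.
- r = 0.95: 1.026/1.033 = 0.993, no saving.

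A simulation of 100,000 trials gave ratios of 1.077, 1.019 and 0.992. With this allowance the 58% above becomes about 57%.

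**The case against.** The strongest reply is that section 4.10 does not say raw end weight is tested. The declared outcome is gain, and the research questions at the end of the Introduction use body weight as a plain label among the clinical outcomes. The sentence in 4.10 can therefore be read as a t-test on gain. The starting weight is then already used by subtraction, and ANCOVA offers little or nothing more. This stands. It limits the large loss to one of two readings, but it does not remove the point: the reader has to supply the definition of gain, because neither 4.9.1 nor 4.10 does.

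A reader might also infer that the result would be biased, or that differences in infant size would hide any effect on gain. The documents support neither. Allocation is random and concealed (4.8.2), so the unadjusted test keeps its type I error, and its standard error already allows for chance imbalance. With no SD, correlation or effect given for weight, an absolute claim cannot be made: at s = 200 g, a 150 g difference still has 56% power on unadjusted end weight. Nor is size at birth the relevant spread; what matters is weight when the protocol starts.

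Finally, covariate adjustment is often left to an analysis plan, and 4.10 does foresee adjusted means. However, the protocol itself chooses the test for this outcome and commits to it, while the model is left optional. That choice is open to comment.

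**Conclusion.** The point holds as a mismatch between outcome and test, with a possible loss of precision. The protocol declares weight gain, leaves it undefined, and commits only to an unadjusted t-test on body weight.

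The size depends on the reading. If end weight is tested, the unadjusted variance is 1/(1−r²) times the adjusted variance before the cost of the slope: 2.8 times at r = 0.80, 5.3 at 0.90 and 10.3 at 0.95. If gain is tested, the difference from ANCOVA is small, about 7%, 2% and 0% of variance at the same correlations. The grams and power figures rest on assumed SDs and correlations.

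The correction is worth making under either reading. With Day-1 weight in the model, end weight and gain give the same treatment estimate, so the ambiguity no longer affects the result.

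**What to change.** In section 4.10, define weight gain as end-of-protocol weight minus Day-1 weight. Replace the t-test for weight with ANCOVA of end-of-protocol weight (or gain) on group and Day-1 weight, and report the adjusted difference with its 95% confidence interval as the stated primary weight analysis. A mixed model on the daily weights with Day-1 weight as a covariate is an acceptable equivalent, provided it is committed to and the contrast at the end of the protocol is named. A hospital factor is optional.

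The definition also needs a single end day. The Abstract and section 3.1 give ten days; the Introduction's hypothesis and sections 4.8.4.1 and 4.8.5.2 give fifteen. These passages must be reconciled.

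The cost is one or two sentences, one degree of freedom (one more if hospital is added) and no new data.
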